### 2.6. Treatments

Each intervention group will be integrated by 10 randomly assigned patients to one of two DMB dosages or placebo. The first arm will have 150 mg of DMB equivalent to 2.8 mg of miraculin + 150 mg of freeze-dried strawberries per orodispersible tablet; the second arm will have 300 mg of DMB equivalent to 5.5 mg of miraculin; and the third arm will contain 300 mg of freeze-dried strawberries per orodispersible tablet as placebo. The three treatments are isocaloric (Table 1). The subjects will be provided with as many tablets as necessary to complete the 3-month intervention period during recurring scheduled visits to the HULP.

### 2.7. Primary Outcome

#### Electrical Taste Perception

Electrical taste perception is evaluated by electrogustometry. Electrical taste testing provides a very accurate means for quantitatively assessing the human taste system [24]. Moreover, functional imaging studies have found that lingual electrical stimulation activates the same brain regions as chemical stimulation [25]. Malnourished cancer patients with taste distortion and consuming the miraculin-based food supplement are expected to improve their taste perception by reducing the taste perception threshold (dB) via electrical stimulation from baseline (v0) to a month after the intervention (v3). The mean of the difference between the scores found between these visits is statistically compared with those found in the rest of the treatments. The evolution of taste perception is also evaluated through the different intervention visits where it is measured (v1, v3, v4, and v5).

The primary sensory system is negatively impacted by a range of diseases and disorders, including early stage cancers [26]. Cancer patients with taste disorders have a 3.36-fold increased risk of malnutrition [27,28]. Malnutrition is related not only to poor prognoses but also to reduced functional status and quality of life [29]. Thus, better food taste perception could enhance food intake and improve malnutrition and the associated risks.

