### 2.12. Data Collection and Management

The study data will be treated following the referenced confidentiality standards and the quality criteria described above. A specific database will be created in Microsoft Office Standard Excel 2013 (Microsoft® Company) using a standardized database creation process. All data collected in the research data collection will be entered by a member of the research team into the original database. This database will be designed with a double-entry system and filters to prevent and detect any type of inconsistency or error. Data will be incorporated based on the ID patient and visit where the results will be collected (vS, v1, v2, v3, v4, v5). The clinical trial Principal Investigator oversaw supervising the database construction. Databases will be stored in the HULP repository within the closed circuit, and RDC will be stored in the nutritionist’s office in a locked filing cabinet.

During the database creation process, a member of the research team will be in charge of notifying the principal investigator of the presence of missing values. These values will be those that for any reason have not been reflected in the RCD by the patient. The member of the research team indicated the affected cells in the database by coloring them yellow with the word “missing”. Once indicated, the sample size of the affected variable will be adjusted for subsequent statistical analysis. In no case will the patient record be deleted, only the missing value that affects the variable.

After incorporating all the data into the database, they will be duly cleaned, avoiding the appearance of symbols (<, >, etc.) that could interfere with the subsequent statistical analysis. The same member of the research team in charge of creating the original database will be in charge of creating a second database in which alphanumeric coding will be given to each variable to guarantee masking during data analysis. If so needed, new variables such as groupings or sums will be created to facilitate comparison between protocol main visits. When the database is finished, the Principal Investigator will oversee sending the Excel file to the Department of Biochemistry and Molecular Biology II (University of Granada) for analysis.

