### 2.13. Statistical Methods

A preliminary study to identify out-of-range values or outliers will be performed. Outliers will be considered those that are greater than the value of the means ± 2 standard deviations. A qualitative descriptive analysis of data will be performed in absolute and relative frequencies and percentages. Quantitative data will be presented as the means ± standard deviations (SD), medians, ranges, percentiles, and percentages. The normality of distribution for each variable will be determined using Kolmogorov–Smirnov and Shapiro–Wilk tests. Levene’s test will be used to evaluate the homogeneity of variances. Parametric or nonparametric tests will be performed depending on whether the variables are normally distributed.

A multivariate analysis of covariance (MANCOVA) for repeated measures will be used to analyze the relationship between a dependent variable and multiple independent variables while controlling for the effects of one or more covariates. A separate analysis of covariance (ANCOVA) on each independent variable controlling for the effects of the covariates will be carried out.

A general linear model (GLM) will be used to model the linear relationship between a dependent variable and one or more independent variables (including continuous, categorical, and binary data). The analysis of the qualitative variables and percentages will be carried out through chi-square (χ^2^) or Fisher’s F analysis depending on the variable sample size.

Specific statistical and bioinformatic software will be used for metabolome, microbiome, and metagenome analyses. This includes PCA, OPLS-DA, analysis of metabolic pathways with mummichog (https://shuzhao-li.github.io/mummichog.org/, accessed on 1 October 2023) and GSEA, PERMANOVA, etc., using the R Project for Statistical Computing. R (https://www.r-project.org/, accessed on 1 October 2023).

Double-sided tests will be applied when needed, and a *p*-value < 0.05 will be considered statistically significant. Data will be analyzed using IBM SPSS Statistics for Windows, version 21.0 (IBM Corp., Armonk, NY, USA) and the R Project for Statistical Computing. R is available as Free Software under the terms of the Free Software Foundation’s GNU General Public License in source code form (https://www.r-project.org/ (accessed on 1 October 2023)).

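### The primary analysis is written as a change score with no baseline covariate and a data-chosen test; a pre-fixed ANCOVA of the v3 threshold on arm and v0 threshold would be more precise at almost no cost

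*Protocol article*

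**What the plan says.** **Primary contrast.** Section 2.7 takes the threshold change "from baseline (v0) to a month after the intervention (v3") and says: "The mean of the difference between the scores found between these visits is statistically compared with those found in the rest of the treatments". No covariate is mentioned there.

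**Models.** Section 2.13 states: "A multivariate analysis of covariance (MANCOVA) for repeated measures will be used". It then adds: "A separate analysis of covariance (ANCOVA) on each independent variable controlling for the effects of the covariates will be carried out". A general linear model follows. The covariates are not named, and none of the three methods is assigned to the primary outcome.

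**Choice of test.** Section 2.13 states: "The normality of distribution for each variable will be determined using Kolmogorov–Smirnov and Shapiro–Wilk tests", and: "Parametric or nonparametric tests will be performed depending on whether the variables are normally distributed". It gives no rule for the case where the two normality tests disagree.

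**Measurement visits.** Section 2.7 places electrogustometry at v1, v3, v4 and v5. Section 4.1 lists it at v0 and Section 4.2.2 at v2. The list for v1 in Section 4.2.1 does not contain it. Sections 4.2.3 to 4.2.5 describe v3 to v5 as similar to v1 and leave the detail to a supplementary file that is not shown.

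**The concern.** The v0 threshold is collected on every patient because it decides eligibility. Subtracting it forces a slope of exactly 1 on baseline. ANCOVA estimates the slope and removes more of the between-patient variation whenever the v0–v3 correlation is below 1. In a trial planned at 10 per arm, with 21 patients completing, that precision is worth having.

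Two wording faults add to this. ANCOVA models a dependent variable, so placing it on the independent variables is wrong as written and leaves the reader unsure what is adjusted. And if normality tests select the method, the primary test is not settled until the data have been seen. Section 2.10 intends the results to size later efficacy studies, so the estimate and its standard error should come from one model named beforehand.

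**Working it through.** **Inputs**
- Baseline electrogustometry, Table 3: 17.16 ± 12.46, 20.5 ± 15.88 and 19.29 ± 15.71 dB, p = 0.909.
- Arm sizes in Table 3: 8, 6 and 7, inferred from the percentages of women (5/8, 2/6 and 6/7 give 13/21 = 61.9%, as stated in Section 5).
- 31 randomised, 10 dropouts, 21 completers (Section 5).
- Correlation rho between v0 and v3: not in the article; assumed 0.3 to 0.9.
- Illustrative difference of 10 dB between two arms: assumed.

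**Reproducing the article's own figure**

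Pooled variance = (7 × 12.46² + 5 × 15.88² + 6 × 15.71²)/18 = 212.7, so SD = 14.58 dB. One-way ANOVA gives F = 0.095 and p = 0.9096, which matches 0.909. The sample size of 30 rests on no calculation, so there is no power figure to reproduce.

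**Precision, equal variances at v0 and v3**
- Change score: variance 2s²(1 − rho).
- Baseline-adjusted: variance s²(1 − rho²).
- Ratio, adjusted to change: (1 + rho)/2.
- Extra interval width of the change score: 1/√ratio − 1.

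| rho | SD change (dB) | SD adjusted (dB) | variance ratio | change interval wider by | power for 10 dB at 10 per arm: change vs adjusted |
|---|---|---|---|---|---|
| 0.3 | 17.3 | 13.9 | 0.65 | 24% | 25.3% vs 36.2% |
| 0.5 | 14.6 | 12.6 | 0.75 | 15% | 33.5% vs 42.5% |
| 0.7 | 11.3 | 10.4 | 0.85 | 8% | 50.8% vs 57.4% |
| 0.8 | 9.2 | 8.8 | 0.90 | 5% | 67.9% vs 72.4% |

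Power is pairwise, two-sided 0.05, by normal approximation.

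A small-sample check used the noncentral t distribution, charging ANCOVA its extra degree of freedom and a penalty for chance baseline imbalance. The difference detectable with 80% power at 10 per arm is 22.4 vs 18.5 dB (rho 0.3), 19.0 vs 16.8 (0.5), 14.7 vs 13.8 (0.7) and 12.0 vs 11.6 (0.8). At rho 0.9 with 7 per arm it is 10.3 vs 10.4 dB: no gain.

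**Test chosen by normality**

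Simulation, 4,000 runs per setting, 7 or 10 per arm, rho 0.5 or 0.8, with a per-arm Shapiro–Wilk rule as one reading of the text:
- The rule switches to Kruskal–Wallis in about 14% of trials with normal errors and in about 36% to 62% with skewed errors.
- ANOVA and Kruskal–Wallis disagree on significance in 2% to 4% of trials with no effect and in 5% to 14% of trials with a 15 dB effect.
- Type I error of the two-stage procedure is 0.045 to 0.056.

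So the rule leaves the primary result open to the choice of test in a minority of trials, but does not visibly inflate the false-positive rate.

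**The case against.** **Covariates are planned.** Section 2.13 does plan ANCOVA and MANCOVA with covariates, and an article may leave the list to an analysis plan. That stands: the omission of a list is no fault in itself. What remains is that Section 2.7 does write a primary comparison, and it is a plain change score.

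**The gain may be small.** Section 6 claims high test–retest reliability for electrogustometry. If rho is 0.8 or more, the gain is 5% in width or less. That also stands as a limit on size. But rho here spans a month of chemotherapy in patients selected on the v0 value, so it may fall below a test–retest figure.

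**A rank test can win.** With skewed errors, rho 0.8 and 10 per arm, Kruskal–Wallis on change reached 93.6% power against 88.7% for ANCOVA. This is a reason to keep a rank version as a sensitivity analysis.

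**Stronger readings that the article does not support.**
- A reader might infer that repeated-measures MANCOVA removes all 10 dropouts. Listwise deletion is nowhere stated. Section 2.12 works variable by variable ("Once indicated, the sample size of the affected variable will be adjusted for subsequent statistical analysis"), and the primary contrast needs only v0 and v3. If every completer has a v3 value, between 21 and 31 patients enter; the actual number is not given.
- A reader might infer that the screen ("Outliers will be considered those that are greater than the value of the means ± 2 standard deviations") deletes only the patients with the worst taste. Section 2.13 speaks of identifying such values, not removing them. Section 3.1.1 sets 0 dB at 8 μA and lowers the intensity after success, so thresholds below 0 dB are possible.
- A reader might infer that a change score leaves baseline differences partly uncorrected. With equal variances and rho below 1 it over-corrects them.
- A reader might infer three unadjusted pairwise tests. The text is equally compatible with an overall three-arm test.

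**Conclusion.** The point holds as one about precision and an unfixed primary test. Section 2.7 specifies a change score without baseline adjustment, and Section 2.13 neither assigns a model to the primary outcome nor words the ANCOVA correctly. The cost is an interval about 24% to 5% wider over rho 0.3 to 0.8, falling to nothing near 0.9 with 7 per arm. These figures assume equal variances at v0 and v3 and a correlation that the article does not report; the dB and power figures also use the pooled SD from the 21 patients implied by Table 3. The normality rule is a fault because it leaves the test open, not because it inflates type I error. No loss of patients by the primary analysis is shown.

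**What to change.** 1. **Reconcile the electrogustometry visits first.** Sections 2.7, 4.1, 4.2.1 and 4.2.2 must agree on when the threshold is measured, and on v0 as the baseline, before it becomes a covariate.
2. **Name one primary model.** ANCOVA with the v3 threshold as dependent variable, arm as factor and the v0 threshold as covariate, in all randomised patients with a v3 value. Correct the ANCOVA sentence in Section 2.13 accordingly.
3. **For the course over time,** use a mixed model on all available post-baseline visits, with v0 as covariate, a simple covariance structure and small-sample degrees of freedom.
4. **Drop the normality rule.** Report a rank or permutation version as a sensitivity analysis.

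The cost is wording and one degree of freedom. The mixed model also assumes data missing at random, is fragile at 7 to 10 per arm, and cannot restore visits that were never made. Section 5 already reports completers, so the change should be dated and made before any comparison of outcomes by arm. If that has already happened, report the adjusted analysis beside the change score and say when it was chosen.

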### 2.8. Secondary Outcomes

Clinical trial variables are to be evaluated from the baseline (v0) to the end of the intervention (v5). The mean of the difference between these visits will be compared with those calculated in the other two treatment groups. The evolution of all clinical trial variables will also be evaluated through the different intervention visits where they will be measured (v1, v2, v3, v4, or v5).

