### 2.10. Sample Size

The sample size is to be established by the researchers owing to the exploratory nature of the study and because there are no previous studies using miraculin-based supplements in cancer patients. At the end of this pilot and to assess the validity of the results, a statistical power calculation will be performed. The obtained results will serve as a basis for establishing the number of participants needed to carry out subsequent efficacy studies.

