Numerous studies carried out in recent years using metagenomic techniques indicate that diet is a powerful agent involved in the establishment of specific microbiota, both in the oral cavity and in the colon [167]. In the present study, we addressed changes in the saliva and stool microbiota in cancer patients. Treatment with DMB and the increase in salivation related to some of its active compounds, such as some amides, as well as the change induced in food intake as a consequence of the improvement of taste and smell alterations, should result in relevant changes both in the salivary microbiome, which should be closer to that of the healthy subject, and in the bacterial pattern of the feces, indicative of the microbiome of the distal colon. Therefore, an improvement in the dysbiosis observed in both saliva and intestine [120,121,122,123,124,125,126,127,128,129] is expected in patients supplemented with miraculin.

One disadvantage of clinical trials is the potential decrease in the number of patients, which may be further reduced due to dropouts throughout the study. However, the primary objective of the pilot clinical trial is to comprehensively assess various parameters affected in cancer patients, who are susceptible to improvement through regular consumption of the miraculin-based food supplement.

The outcomes of this pilot clinical trial are anticipated to demonstrate whether the regular consumption of a miraculin-based food supplement, whose active principle is the miracle berry extract DMB, has a positive effect on taste distortion and the nutritional status of malnourished cancer patients undergoing active antineoplastic treatment and to determine the dosage at which maximum benefits are achieved.

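### One flat p < 0.05 over more than 60 unranked secondary variables does not support the conclusions on nutritional status and the restated primary objective in section 6

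*Protocol article*

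**What the plan says.** Section 2.7 of the protocol article names one primary outcome: the change in electrical taste threshold from v0 to v3, compared between treatments.

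Section 2.8 treats all secondary variables alike. Each is assessed from v0 to v5, and "The mean of the difference between these visits will be compared with those calculated in the other two treatment groups". Beyond that endpoint comparison, "The evolution of all clinical trial variables will also be evaluated through the different intervention visits". Sections 2.8.1 to 2.8.10 list the domains without ranking them.

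Section 2.13 plans a repeated-measures MANCOVA and adds: "A separate analysis of covariance (ANCOVA) on each independent variable controlling for the effects of the covariates will be carried out". It sets one threshold for every test ("p*-value < 0.05 will be considered statistically significant"), with sidedness left loose ("Double-sided tests will be applied when needed").

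Section 2.10 explains the absence of a sample-size calculation: the number was set by the researchers "owing to the exploratory nature of the study". It says the results will help fix the number of participants for later efficacy studies.

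Section 6 speaks differently. It states that "the primary objective of the pilot clinical trial is to comprehensively assess various parameters affected in cancer patients". It also expects the outcomes to demonstrate whether regular use of the supplement "has a positive effect on taste distortion and the nutritional status of malnourished cancer patients undergoing active antineoplastic treatment", and to identify the dose with the greatest benefit.

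**The concern.** Two things do not fit together.

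The first is the objective. A trial whose primary outcome is a single electrogustometry change cannot also have the assessment of the whole parameter set as its primary objective. A reader of section 6 would not know which result decides the trial.

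The second is the link between the testing rule and the announced conclusion. Nutritional status and its supporting measures are secondary. A flat 0.05 over a long, unranked list will often yield nominally significant results when nothing is happening. Section 6 nevertheless presents the trial as able to settle whether nutritional status benefits. It comes closest to reading panel results as benefit when it says that any change in the erythrocyte fatty acid profile would point to better nutritional status.

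What is at stake is interpretation. An isolated secondary p < 0.05 could be reported as an effect on nutrition, inflammation or quality of life even if electrogustometry shows nothing. Effects picked out because they were significant also tend to be too large, which matters because 2.10 intends to size later studies from these results.

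**Working it through.** The article gives no number of tests, no familywise error rate and no power figure, so there is no stated figure to reproduce.

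**1. How many variables?** A conservative count uses only variables named individually in section 2.8 and the methods in section 3:

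| Domain | Count |
|---|---|
| Taste strips (total and four qualities) | 5 |
| Smell | 1 |
| Anthropometry | 5 |
| Bioimpedance | 14 |
| Ultrasound | 8 |
| Grip strength | 1 |
| Timed up and go | 1 |
| QLQ-C30 scales and items | 15 |
| Cytokines and cachexia factors, duplicates removed | 14 |
| **Sum** | **64** |

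Adding GLIM status (1), macronutrient intake (9), physical activity (2), the taste and smell survey (3), gastrointestinal symptoms (6), general biochemistry (30), fatty acids (6), oxidative stress (2) and antioxidant defence (10) gives 64 + 69 = 133. Micronutrient intakes, food-frequency items, blood count, metabolomics and microbiota are still left out. The calculations use 60 and 130.

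**2. Independent tests, one per variable.** P(at least one false positive) = 1 − 0.95^m.
- m = 60: 1 − 0.95^60 = 95.4%; expected number 60 × 0.05 = 3.
- m = 130: 1 − 0.95^130 = 99.9%; expected number 130 × 0.05 = 6.5.

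**3. Correlated tests.** The variables are correlated, but the article does not say how strongly. I assume a common correlation from 0 to 0.7, normally distributed changes, no true effect, 10 patients per arm (section 2.6), one time point, and all variables coded so that higher is better. Two events were simulated: at least one three-arm F test with p < 0.05, and at least one two-sided p < 0.05 in favour of either DMB dose over placebo (pooled-variance t test).

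| Correlation | Any F test, 60 variables | Any result favouring DMB, 60 variables | Any F test, 130 variables | Any result favouring DMB, 130 variables |
|---|---|---|---|---|
| 0 | 96% | 94% | 99.9% | 99.7% |
| 0.3 | 85% | 67% | 97% | 82% |
| 0.5 | 67% | 51% | 83% | 63% |
| 0.7 | 46% | 36% | 57% | 42% |

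These figures carry simulation error; repeat runs differ by up to about 3 percentage points. The expected number of significant F tests stays at 3 (or 6.5) whatever the correlation. Arms of 8, 6 and 7, the split that the Table 3 percentages fit for the 21 completers, give nearly the same results.

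**4. Effect of the test chosen.** If all three pairwise contrasts are tested for each of 60 variables, 60 × 3 × 0.05 = 9 false positives are expected. The chance of at least one, in any direction, is then about 93% at correlation 0.5. That figure includes placebo beating DMB and one dose beating the other, so it does not measure the chance of a spurious benefit.

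**The case against.** The strongest reply is that ranking and error control for secondary outcomes are commonly left to the analysis plan. That plan is not shown, and a journal article condenses the full protocol. This stands: a missing multiplicity method is not in itself an error here, and the point does not rest on it.

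A reader might infer that the plan treats any significant secondary result as proof of benefit. The article does not say so. Section 2.13 defines when a result is called significant and gives no rule for declaring efficacy; 2.7 names one primary outcome; 2.10 calls the study exploratory; and the word pilot recurs throughout. Section 6 asks whether there is an effect and does not assert one. Nor does 2.10 say that these results will choose the endpoint of a later trial; it mentions only the number of participants.

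A reader might also infer that a chance benefit is almost certain. That would need near-independent variables, or the longer count with weak correlation. Many variables are close to duplicates: weight and BMI in an adult of fixed height, or phase angle and the resistance and reactance from which it is derived. Section 2.13 names MANCOVA and ANCOVA rather than pairwise t tests, so the F-test figures are the fairer guide to the number of false positives. For the metabolome and microbiome it already plans multivariate methods.

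These replies reduce the size of the problem. They do not remove the contradiction between sections 2.7 and 6, or the gap between a flat 0.05 and the conclusion section 6 announces. Both are in the text shown.

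**Conclusion.** The point holds in limited form. The article states two incompatible accounts of the primary objective, and it announces a conclusion about a secondary outcome that its single significance threshold cannot carry.

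With no true effect and 60 variables, at least one significant F test has a chance of about 46% to 96%, and at least one nominally significant result favouring DMB over placebo about 36% to 94%, as the correlation falls from 0.7 to 0. With 130 variables the second range is about 42% to 99.7%. A spurious benefit is thus more likely than not up to a correlation of about 0.5.

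These figures rest on an assumed common correlation, one test occasion per variable, and 10 patients per arm. The visit-by-visit evaluations, which are not counted here, would add further opportunities for chance findings.

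**What to change.** 1. In 2.8 and 2.13, state that all secondary comparisons are exploratory and are reported as differences versus placebo with 95% confidence intervals. State also that no efficacy claim will rest on an isolated p < 0.05.
2. In 2.13, apply false-discovery-rate control within each of the cytokine, fatty-acid, metabolomic and microbiota panels. The data availability statement says that saliva, plasma and fecal analyses were still under way, so this can be fixed before those results are read.
3. In section 6, restate the primary objective as the electrogustometry change defined in 2.7, and replace *demonstrate whether* with *estimate* for nutritional status.

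A formal gatekeeping scheme with a key secondary endpoint is not needed in a 30-patient pilot.

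The cost is wording and a routine adjustment in the panel analyses; no new data are required. The downside is small: isolated significant secondary results can no longer be presented as shown effects.
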